#### Secondary outcome measures

Infant development will be assessed at 12 months (and at 6 and 8 months) using the ASQ3. These questionnaires assess development in five domains: communication, gross motor, fine motor, problem-solving and social–personal. The ASQ3 has been successfully applied in community-based, low-resource settings and has been found to be feasible in South Africa.^54 55^

The acceptability of each phase of the intervention will be assessed based on the Theoretical Framework of Acceptability.^56^ This framework includes the following criteria: affective attitude, burden, ethicality, intervention coherence, opportunity costs, perceived effectiveness, and self-efficacy. These criteria will be assessed by means of questionnaires specific to each intervention theme, followed by focus group discussions (FGDs) in a subsample of participants to expand on core themes identified.

Feasibility of each phase of the intervention will be assessed by determining whether the developed intervention is implementable in this context, has potential to work, as well as how it could be improved for future use and in other settings. We will follow the MRC guidance on process evaluation of complex interventions.^57^ The evaluation will focus on implementation, mechanisms of impact and context.

Compliance will be assessed by counts (eg, login frequency on app, delivery of messages and monitoring of phone calls using a log) and by discussions with the HHs.Intervention dose will be monitored by recording the frequency and duration of contact as well as the topics of conversation between participants and HHs or feedback given to participants using the logs.To understand the mechanisms through which the intervention brings about change in specified outcomes, women’s experiences of receiving the intervention, contact with HHs and the app will be assessed using questionnaires and focus groups at the close of each intervention phase. We will also use the secondary outcomes (process data) to determine whether individual proposed pathways of impact are effective prior to analysing trial outcomes.In considering the context, identification of factors that might act as barriers or facilitators to intervention implementation or effects will be assessed. This will include local and national policy, local service configuration and provision, and sociodemographic and environmental factors of the participants. Our approach to assessing context will be through a combination of policy mapping, quantitative data collection and longitudinal consultation with the CAG.

Maternal breastfeeding self-efficacy will be assessed every 2 months from 0 to 6 months using the Breastfeeding Self-Efficacy Short Form.^58^ This comprises 14 questions, each with a 5-point Likert response scale ranging from 1=not at all confident to 5=very confident. The higher the final aggregate score (which has a range of 14–70), the higher the level of breastfeeding self-efficacy.

Exclusive breast feeding will be assessed every 2 months from 0 to 6 months by asking mothers whether they are currently breast feeding and if not, at what infant age did they stop breast feeding and why they stopped breast feeding. They will also be asked if they are giving their infant anything other than breastmilk, and if so, why.

Weight and length will be measured by trained research staff at baseline and 12 months (and at 4 and 8 months). Weight-to-length ratio (kg/m) will then be calculated to estimate anthropometric changes in body composition. At 12 months, DXA scans will be performed by a trained technician. Whole-body measurements of fat mass and fat-free mass will be extracted for use in analyses. FMI (kg/m^3^) will be calculated from these estimates to describe adiposity.

Health literacy will be assessed at 6 and 12 months using the parent version of the Health Literacy Questionnaire,^59^ which covers nine areas of health literacy including functional health literacy and has been validated in high-income and low-to-middle-income countries.

Various aspects of maternal mental health will be assessed at baseline, 4 and 12 months. The PCL-5^60^ will be administered whereby rating scale descriptors include: ‘not at all’, ‘a little bit’, ‘moderately’, ‘quite a bit’ and ‘extremely’. A total symptom severity score is calculated by adding up the item scores, which range from 0 to 80. The cut-off for PTSD that will be used in this study was 31. The EPDS^61^ will be used to detect postnatal depression. Scores for each item range from 0 to 3 on a Likert scale and are added together to obtain an overall total. Scores of 7–13 indicate mild depression, 14–18 moderate and 19–30 severe depression. The ACE Questionnaire^62^ will assess childhood abuse, neglect and household challenges. A score from 0 to 10 is calculated based on how many types of events were experienced before 18 years old. The ASQ will be administered to assess stressful life events. An additional nine items about social support will be included. The Postpartum Bonding Questionnaire^63^ will be used to detect early mother–infant bonding. It consists of four subscales ‘impaired mother/infant bonding’, ‘rejection and anger’, ‘anxiety about care’ and the ‘risk of abuse’. These questions are rated on a 6-point Likert scale, ranging from 0 (always) to 5 (never).

Infant adherence to movement guidelines will be assessed every 4 months using accelerometery. Seven-day, 24-hour wrist worn accelerometery data (Axivity-AX3 worn on both mother and infant) will be collected, downloaded (omgui, Open Movement, UK), auto-calibrated and processed. Data is summarised to generate average acceleration (mg) per 5 s interval, as well as overall time (hourly and weekly) spent in varying intensities of activity, which will allow for determination of adherence to movement guidelines and changes in activity levels over the intervention period.

Mother–infant interactions will be measured during play using first-person observation and behavioural analysis every 4 months. Mother–infant interactions have primarily been measured using questionnaires or third-party observation, yet these measures are limited by their subjectivity and intrusiveness. First-person observation using headcams—small cameras which are attached to headbands on both infants and mothers for a period of time while interacting at home—provide a first-person view of the interaction from both infant and mother perspectives with more naturalistic and detailed measures. These headcams have been piloted in South Africa and were found to be largely acceptable and feasible in this context.^64^ Headcam measures will be collected during at least five, 3–5 min play interactions over the course of a week. Headcam observations will be coded using Noldus Observer XT software. An event-based coding framework will be used to categorise second-by-second key maternal and infant behaviours, that is, touch, play, facial expressions, hand movement, and gaze. This allows for determination of the probability of certain behaviours preceding or following another, associations between maternal/infant measures and these behaviours, and synchrony between mothers and infants as a potential indicator of sensitivity and responsiveness.

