### Study design

The PLAY Study was designed following the Standard Protocol Items: Recommendations for Interventional Trials 2013 statement.^49^ Mother–infant pairs (n=210) will be recruited starting in the third quarter of 2022 until the second quarter of 2023, and individually randomised into two groups (total n after expected attrition=150, n=75 in each group) using simple 1:1 randomisation generated by Stata V.17. The intervention will last from birth to 12 months, with main assessments made when the infants are 0, 6 and 12 months of age. The trial will consist of a standard of care arm and an intervention arm—see figure 1. Data collection teams will be blinded to randomisation at baseline and during primary outcome assessments, and separate data collection teams will collect baseline compared with primary outcome data. Blinding will be maintained by the data manager and broken only for a priori defined analyses (figure 2). Randomisation into either group will be generated by the data manager only after recruitment and baseline assessments are completed, whereafter participants will be assigned to the intervention delivery teams accordingly (intervention delivery teams will thus not be blinded). Intervention delivery teams will work separately and independently of each other, and of data collection teams. The trial is due to be completed in the second quarter of 2024.

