### Outcome measures

Data collection will be conducted by independent, trained research assistants. The primary outcome measure is efficacy of the intervention in improving maternal self-efficacy at 12 months. Secondary outcomes will estimate efficacy of the intervention in improving infant development at 12 months, and will assess the feasibility and acceptability of the intervention at 6 and 12 months, as well as interim outcomes to determine mechanisms of impact (figure 2).

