#### Secondary outcomes at 6 months

Breastfeeding self-efficacy from 0 to 6 months compared between intervention and control groups.Exclusive breast feeding from 0 to 6 months compared between intervention and control groups.Feasibility and acceptability of the breastfeeding intervention.

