### Sample size

Given expected attrition of 30%, recruiting 210 mother–infant pairs should yield a final sample size of 150 mother–infant pairs, which will be divided into 2 groups (n=75 each). A sample size of 150 mother–infant pairs divided into 2 groups (n=75 each; control and trial group) will allow for 99% power to detect efficacy of the intervention based on maternal self-efficacy data assessed in the piloting phase of the behavioural feedback intervention (data not yet published).

Attrition will be minimised by maintaining regular contact with both groups, by recruiting participants who plan on remaining in Soweto, and by using a flexible and versatile delivery approach including in-person visits, app-based content, telephonic sessions, mobile messaging and site visits.

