## Discussion

If found to be feasible, acceptable and successful, these findings could lead to implementation of the intervention on a larger scale. Particularly, implementing intervention content within primary healthcare services, and linkage with existing digital solutions (such as MomConnect in South Africa), would allow for dissemination of the health literacy components of this intervention nationally. Furthermore, the PLAY Study app has the potential to be developed further and made into an accessible app for all mothers. All of this content aligns with the Nurturing Care Framework and WHO guidelines and is therefore relevant at a national policy level, as well as internationally. Additionally, engagement with the community and dissemination of findings to participants and other stakeholders provides opportunities for knowledge mobilisation and therefore greater impact. There is potential to transfer the intervention to other LMICs and high-income countries; however, since this content was designed with the Soweto community to be contextually relevant, adjustments would need to be made to ensure the feasibility and acceptability in other contexts. Certain aspects of the intervention, such as the accelerometery and headcam assessments and feedback, are more complex and would require funding and training to implement on a larger scale, yet the concept of providing feedback using some of the other assessments such as development and growth can feasibly be incorporated into digital platforms or the PLAY Study app for scaling up.

The PLAY Study relies to some extent on the availability of cell phone or computer access for the delivery of intervention content, which may be limiting in the Soweto setting. However, we will attempt to mitigate this by making the app data free, by making the app available on multiple platforms (web, mobile, android, Apple etc) and by continuously consulting with the CAG to ensure we come up with appropriate solutions if we encounter lack of access. Findings from this study are relevant to a socioeconomically disadvantaged group of mothers, and thus cannot be extrapolated to higher income settings or different population groups. This study does not specifically include fathers due to the low prevalence of caregiving fathers in this context. Future studies directed at both parents or at other caregivers would need to be adjusted for those population groups.

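### Each phase's acceptability result leaves out intervention mothers who left before that phase closed, and the article describes no assessment at the point of leaving

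*Protocol article*

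**What the plan says.** Acceptability stands beside efficacy and feasibility in all three aims. Under Outcome measures, the secondary outcomes "will assess the feasibility and acceptability of the intervention at 6 and 12 months". The 6-month list contains "Feasibility and acceptability of the breastfeeding intervention", and the 12-month list has the matching item for health literacy and behavioural feedback.

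The method is under Secondary outcome measures. It uses an acceptability framework whose criteria include affective attitude, burden and opportunity costs: "These criteria will be assessed by means of questionnaires specific to each intervention theme, followed by focus group discussions (FGDs) in a subsample of participants". Later in the same section, under mechanisms of impact, women's experiences of the intervention, of the health helpers and of the app "will be assessed using questionnaires and focus groups at the close of each intervention phase".

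On losses, the Sample size section says: "Given expected attrition of 30%, recruiting 210 mother–infant pairs should yield a final sample size of 150 mother–infant pairs". Study design gives the allocation: mothers are "individually randomised into two groups (total n after expected attrition=150, n=75 in each group) using simple 1:1 randomisation". The Data analysis plan specifies intention to treat for efficacy. For feasibility and acceptability it names only qualitative and quantitative methods.

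On use of the result, the Discussion says: "If found to be feasible, acceptable and successful, these findings could lead to implementation of the intervention on a larger scale".

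**The concern.** An end-of-phase questionnaire reaches only mothers who are still in the study when the phase ends. A mother who left earlier gives no rating for that phase, and the article describes no step that asks for her view when she goes. Several of the criteria being rated are plausible reasons for going, so the missing ratings are plausibly related to the outcome itself and the ratings that remain would tend to look better.

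This is more than a question of analysis. A denominator or missing-data rule can be settled later in a statistical analysis plan, but views that were never collected cannot be recovered there. The timing of collection is a design choice, and the article states it.

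At stake is the reading of an outcome that appears in every aim and in the condition for wider implementation. The efficacy comparison is not affected.

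**Working it through.** **Inputs from the article:** 210 recruited, 1:1 allocation, 30% expected attrition, 150 retained (75 per group), acceptability assessed at 6 and 12 months.

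**Assumptions:** the intervention arm has 210 / 2 = 105 mothers (approximate, because randomisation is simple); the overall attrition applies equally to that arm; the 30% is cumulative to 12 months. The article gives no attrition by arm or by time.

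**1. The plan's own figure.** 210 × (1 − 0.30) = 147, against 150 stated. The loss implied by going from 210 to 150 is 60 / 210 = 28.6%. The stated figure is reproduced to within rounding.

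**2. Mothers without a 12-month rating.**
- At 28.6% loss: 105 − 75 = 30.
- At 30% loss: 105 × 0.30 = 31.5.

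So about 30 to 32 of 105. The number missing at 6 months cannot be larger, and is smaller unless every loss falls in the first half of the study.

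**3. Mothers never rated.** Only those who leave before the 6-month assessment miss both scoring points. With 31.5 losses in total:

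| Share of losses before month 6 (assumed) | Never rated | Share of 105 |
|---|---|---|
| 0% | 0 | 0% |
| 25% | 7.9 | 7.5% |
| 50% | 15.8 | 15% |
| 75% | 23.6 | 22.5% |
| 100% | 31.5 | 30% |

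Under a constant dropout rate (assumed), retention at 6 months is √0.70 = 0.837. The share never rated is then 1 − 0.837 = 16.3%, or 105 × 0.163 ≈ 17 mothers.

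**4. Hypothetical effect on the 12-month result.** The article defines no acceptance percentage, so both the yes/no measure and the 85% among those who stay are assumed. Mothers staying: 105 × 0.70 = 73.5, of whom 73.5 × 0.85 = 62.5 accept.
- No leaver accepts: 62.5 / 105 = 59.5%.
- Half of the leavers accept: (62.5 + 15.75) / 105 = 74.5%.
- All leavers accept: (62.5 + 31.5) / 105 = 89.5%.

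Against a reported 85%, the extremes are an overstatement of 85 − 59.5 = 25.5 points and an understatement of 89.5 − 85 = 4.5 points.

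**The case against.** The strongest case against has five parts.

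- **Two scoring points.** A reader might infer that the whole 30% is never rated. The article does not support that: a mother who leaves between months 6 and 12 can be rated for the breastfeeding phase, and the 30% refers to both arms together. This part stands, and the point is limited accordingly.
- **The sentence on timing is about something else.** The end-of-phase wording concerns women's experiences under mechanisms of impact, not the acceptability framework as such. True, but Outcome measures independently places acceptability at 6 and 12 months, so the timing does not depend on that sentence.
- **It argues from silence.** A condensed article may leave exit procedures to the full protocol and denominators to the analysis plan. That is fair for the denominator. For collection, the article states when ratings are taken and mentions nothing earlier. If the full protocol has an exit form, citing it resolves that part.
- **The size is invented.** The 85% and the yes/no measure are indeed assumptions, and the 25-point gap is the extreme at which no leaver accepts. A reader might take it as an expected bias, but nothing in the article supports it as a prediction. Mothers may also leave for unrelated reasons: the eligibility criteria and the attrition measures both refer to plans to remain in Soweto, so moving away is an anticipated cause. The direction of bias is likely, not certain.
- **Disengagement is already visible.** Compliance, dose and app use are logged throughout, adherence is assessed every 4 months, and retention is discussed weekly with the health helpers. This answers the question for feasibility. For acceptability it does not, because logs record use and not how a mother rates burden or cost. The community advisory group is a separate body set up before the trial.

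**Conclusion.** The point holds in a limited form. Each phase's acceptability result excludes intervention mothers who left before its close: about 30 to 32 of roughly 105 at 12 months if the overall attrition applies to that arm, and probably fewer at 6 months. The share never rated lies between 0% and 30% depending on when losses occur, and is about 16% under constant dropout. The result is probably biased upward, because some of the rated criteria are plausible reasons to leave. How far cannot be known from the article; the range of about 60% to 90% is a bound under assumed inputs. The Discussion sets no acceptability threshold for scale-up, so no decision rule is shown to fail. This is a worthwhile, inexpensive improvement to a secondary outcome and not a flaw in the efficacy analysis.

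**What to change.** 1. Have the independent research assistants give a short form of the acceptability items, with the reason for leaving, at the last contact or a withdrawal call, to mothers who agree to answer. Contacts every 2 months are already scheduled in both arms.
2. Invite some early leavers to the focus-group subsample.
3. Report each phase's acceptability beside the number allocated to the intervention arm. Keep the completers' figure as the main result and add a sensitivity lower bound that counts leavers as not accepting. Show separately those who left for unrelated reasons such as moving away, so that they are not read as rejections.
4. Leave feasibility as planned, since its data accrue throughout.

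The cost is a few extra questions for mothers who consent to them, and possibly a less favourable reported figure. Intervention delivery and the efficacy analysis do not change.

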### Promotion of early learning through play

Infant movement behaviours have been identified as important for early childhood growth and development.^14^ Three categories of movement behaviours are of key importance: physical activity, sleep and sedentary behaviours.^14^ These three behaviours are contingent on each other to make up a 24-hour day, yet have independent health implications and thus independent recommendations, which should all be met for optimal health. Guidelines for these behaviours in the first few years of life encourage tummy time and active play, sufficient and regular sleep, and minimisation of activities that require infants to be restrained (eg, car seats, strollers, walkers).^14–16^ Play is defined as intrinsically motivated activities done for recreational purposes and enjoyment. Play is how children learn, explore, engage in physical activity and motor development, develop socially, emotionally and cognitively, and bond with caregivers.^17 18^ Outdoor play is particularly encouraged due to its beneficial effects on both physical activity and development.^19^ Additionally, interactive and stimulating play (such as reading, singing and playing with other adults or children) is encouraged to promote development^20^ and also supports early learning.^6^

Formative research in South Africa has determined that higher intensity movement was associated with earlier attainment of developmental milestones^21^ and with taller stature and lower abdominal adiposity.^22^ However, the majority of infants in South Africa were not meeting recommended 24-hour movement guidelines.^23^ When using synchronous 24-hour accelerometery worn by mothers and infants, we showed that increased physical activity among mothers while caring for their infants was associated with increased infant movement during the same period of time.^24^ This highlights the important role of the mother in infant movement behaviours, and thus growth and development. Interactive play is particularly important for promotion of parent–child bonding, offering an ideal opportunity for parents to engage with their children through stimulating activities which encourage movement, and in turn promote cognitive, emotional and social development. Stimulation interventions in LMICs have been shown to improve home caregiving environments, mother–child interactions and maternal health literacy around ECD.^25^

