### Hypotheses

Using behavioural feedback and content provision to support mothers in their ability to be responsive, promote early learning in the home, understand and engage with their infants’ health behaviours (specifically movement behaviours interactions), in conjunction with supporting mothers’ mental health, will result in improved maternal self-efficacy, and therefore better infant development in the first year of life.Supporting mothers with breastfeeding content, guidance and referrals to lactation specialists in the first 6-month postpartum will increase self-efficacy, and thus improve breastfeeding exclusivity.Proving mothers with access to resources, content and activities to support their infant’s play and development will increase their health literacy, and thus encourage play and promote development.

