#### Secondary outcomes at 12 months

Infant development at 12 months compared between the intervention and control groups using the Ages and Stages Questionnaire (ASQ3).Feasibility and acceptability of the health literacy and behavioural feedback intervention.Change in infant weight to length ratio compared between intervention and control groups.Infant fat mass index (FMI) (assessed using dual X-ray absorptiometry (DXA) fat mass divided by length) compared between intervention and control groups.Change in maternal health literacy from 6 to 12 months compared between intervention and control groups.Change in maternal mental health from 0 to 12 months compared between the intervention and control groups.Infant movement behaviours compared between intervention and control groups.Mother–infant interaction styles compared between intervention and control groups.

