### Data analysis plan

The efficacy of the intervention will be assessed using intention to treat analysis. Secondary outcome data will be compared between the intervention and standard of care arms using Student’s unpaired t-tests. Focus will be placed on the primary efficacy outcome (maternal self-efficacy) due to limited power for secondary outcomes, which will therefore be treated with caution and presented using point estimates and precision (95% CI). Sensitivity analyses will include comparing baseline characteristics between intervention and standard of care arms, examining the effect of intervention dose on outcome data and stratifying analyses by sex.

The feasibility and acceptability of the intervention at each phase will be assessed using qualitative and quantitative methods. FGDs will be transcribed and coded line by line, and data will be grouped according to common themes. Themes will be sorted into subthemes and continually reviewed to identify an overarching narrative to identify key findings from each FGD.

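### Weight-to-length ratio in kg/m still depends on length, so a between-arm difference in its change cannot separate linear growth from body composition

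*Protocol article*

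**What the plan says.** Under Secondary outcomes at 12 months, the protocol article lists "Change in infant weight to length ratio compared between intervention and control groups". Under Secondary outcome measures it gives the timing, "Weight and length will be measured by trained research staff at baseline and 12 months (and at 4 and 8 months"), and then the index and its purpose: "Weight-to-length ratio (kg/m) will then be calculated to estimate anthropometric changes in body composition". No standardisation for age or sex is given for this outcome.

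The Data analysis plan states: "Secondary outcome data will be compared between the intervention and standard of care arms using Student’s unpaired t-tests". It mentions no adjustment for length. It does say that secondary outcomes have limited power, are to be interpreted cautiously, and will be shown as estimates with 95% confidence intervals.

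Two other places bear on the point:

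- The introduction (Promotion of early learning through play) reports from formative research that more intense infant movement went together "with taller stature and lower abdominal adiposity".
- Adiposity is also measured directly by DXA, at 12 months only. The outcome list words that index as "Infant fat mass index (FMI) (assessed using dual X-ray absorptiometry (DXA) fat mass divided by length"), whereas Secondary outcome measures gives its unit as kg/m^3.

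**The concern.** The plan gives the ratio a specific job, to show changes in body composition. An index can do that only if infants of different length but the same build get about the same value. Weight usually rises more than in proportion to length, so dividing by length once leaves part of the stature effect in the result.

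A difference between arms could then come from linear growth, from relative weight, or from both, and the planned t-test cannot tell these apart. A null difference could not be read as no change in body composition, nor a positive one as more fat. DXA does not fill the gap: it is done once, so the ratio is the only listed outcome that follows body composition over time. The article also says that secondary outcomes will be used to judge whether the proposed pathways work before the trial outcomes are analysed, so a misread ratio could carry into that step.

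**Working it through.** **Plan's own figure.** There is none to reproduce: the documents give no mean, SD or expected difference for this ratio. All infant sizes, exponents and fat shares below are assumptions.

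**1. Scaling.** Let W be weight and L length, with W proportional to L^p at unchanged build. Then W/L is proportional to L^(p-1), which rises with length whenever p > 1 and is independent of length only at p = 1.

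**2. Effect of 1 cm at the same build.** Assume 9.5 kg and 0.75 m at 12 months, so W/L = 9.5/0.75 = 12.67 kg/m. The new ratio is 12.67 x (0.76/0.75)^(p-1). The fat loss that restores the old ratio is the rise times 0.76 m.

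| p | Rise in W/L (kg/m) | Rise (%) | Fat loss that cancels it (kg) |
|---|---|---|---|
| 1.5 | 0.084 | 0.66 | 0.064 |
| 2 | 0.169 | 1.33 | 0.128 |
| 2.5 | 0.254 | 2.01 | 0.193 |
| 3 | 0.340 | 2.68 | 0.258 |

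If body fat is 20% to 30% of weight, 0.064 to 0.258 kg is about 2% to 13% of fat mass.

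**3. Effect of 1 cm at unchanged weight.** 9.5/0.76 - 9.5/0.75 = 12.50 - 12.67 = -0.17 kg/m. The ratio falls. The sign of a length effect therefore depends on how much weight comes with the length.

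**4. Correlation with length between infants.** A second set of assumptions: weight 9.3 kg (SD 1.0), length 0.75 m (SD 0.026), weight-length correlation r. The coefficients of variation are c_W = 1.0/9.3 = 0.1075 and c_L = 0.026/0.75 = 0.0347. To first order, the correlation of W/L with L is

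(r c_W - c_L) / sqrt(c_W^2 + c_L^2 - 2 r c_W c_L).

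- r = 0.5: (0.0538 - 0.0347)/0.0951 = 0.20.
- r = 0.7: (0.0753 - 0.0347)/0.0869 = 0.47.

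The numerator is positive for any r above c_L/c_W = 0.32. For W/L^2, simulation on the same assumptions gives -0.16 at r = 0.5 and 0.08 at r = 0.7.

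**5. Growth over the year.** Assume 3.2 kg and 0.50 m at birth. The ratio goes from 3.2/0.50 = 6.4 to 12.67 kg/m. The implied exponent is ln(9.5/3.2)/ln(0.75/0.50) = 2.7, well above 1. Even at constant W/L^2 the ratio would reach (3.2/0.50^2) x 0.75 = 9.6 kg/m. This growth is common to both arms, so it says how far the index is from being length-free over this age range. It is not a measure of bias.

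**6. Size against precision.** On the assumptions of step 4, the SD of W/L is about 12.4 x 0.087 to 12.4 x 0.095, or 1.08 to 1.18 kg/m. With 75 per arm, the 95% half-width for a difference in the 12-month ratio is 1.96 x SD x sqrt(2/75) = 0.35 to 0.38 kg/m. A 1 cm difference at constant W/L^2 gives (9.3/0.75^2) x 0.01 = 0.165 kg/m, under half of that.

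**The case against.** A reader might infer that the trial expects taller and leaner infants, and that these two effects will cancel in the ratio. The documents do not support that. The stated hypothesis is that the intervention "will result in improved maternal self-efficacy, and therefore better infant development in the first year of life"; the other hypotheses concern breastfeeding, health literacy and play. The statement on stature and adiposity is a background association without a magnitude, and its adiposity part is abdominal. Cancellation also needs weight to rise more than proportionally with length: at unchanged weight, extra length lowers the ratio (step 3), the same direction as fat loss. For the same reason it would be wrong to say that a gain in length alone would look like added fatness.

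A reader might also infer bias from the near-doubling of the ratio over the year, or from the lack of age and sex standardisation. Allocation is randomised 1:1, both arms are measured at the same ages, and analyses stratified by sex are planned. The omission costs precision and interpretability only.

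It is fair to add that the effect in step 6 lies within sampling error, that a 1 cm difference is large (0.38 SD on the assumed SD of 2.6 cm), that at r = 0.5 W/L^2 is nearly as length-dependent as W/L with the opposite sign, and that DXA measures fat directly. All of this limits the consequence. It does not make the ratio an estimate of change in body composition: DXA has no baseline, and cautious reading because of low power does not separate two mixed quantities.

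**Conclusion.** The point holds as a limited one. The ratio in kg/m is not independent of length, so a between-arm difference in its change cannot do what the article says it is for. The direction rests on one assumption, that weight rises more than proportionally with length at the same build. The size (0.08 to 0.34 kg/m per centimetre) rests on assumed infant sizes and exponents.

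If the background associations with stature and abdominal adiposity carried over to the trial, and that assumption held, they would pull the ratio in opposite directions. Whether they would cancel depends on magnitudes that the documents do not give. This is one secondary outcome and no primary conclusion depends on it, but the improvement is cheap and worth making.

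**What to change.** In Secondary outcomes at 12 months and in Secondary outcome measures:

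- Make the outcome the change from baseline to 12 months in age- and sex-standardised weight-for-length z-score, or the 12-month z-score adjusted for its baseline value. Either keeps the contrast with baseline, which a 12-month z-score alone would lose. Name the growth reference used.
- Report length-for-age z-score beside it, so that linear growth and relative weight are seen separately.
- Keep kg/m as a descriptive measure only.

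Separately, reconcile the two descriptions of the DXA fat mass index (divided by length in one place, kg/m^3 in the other), because it will be read alongside this outcome.

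The cost is wording and a standard calculation. Weight and length are already measured, sex is already needed for the stratified analyses, and age follows from the visit and birth dates. The downside is slightly less direct comparability with earlier reports that used kg/m; the descriptive kg/m figures cover most of that.
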